#### Statistical analysis

Data will be analysed according to intention to treat, but if there is a non-compliance and dropout of more than 10%, we will also perform the statistical analysis without those with non-compliance. Demographic data will be presented as counts and percentages for categorical variables and continuous variables will be presented as mean and standard deviation. Data will be tested for normality using QQ-plots and will be log transformed if applicable. For all statistical analysis a level of statistical significance will be defined as 0.05. The primary outcomes PE, FGR and GDM, will be assessed by comparing the event rates in the two groups using a chi-square test and results will be presented as absolute and relative risks along with 95% confidence intervals (Cl). A similar approach will be used for categorical secondary outcomes. A multiple linear regression model will be used to adjust for indifferences in baseline characteristics. The 25(OH)D level will be assessed by comparing the mean in the two groups using students t-test. The same approach will be used for continuous secondary outcomes. Linear regression models will be used to assess continuous variables such as serum levels, blood pressure and biological changes in the placentas.

Subgroup analysis will be performed for the following subgroups:25(OH)D level at enrolment (< 50, 50–75, > 75)Parity (nulliparous vs primiparous and multiparous)EthnicityBMI (Body Mass Index) (≥ 20- < 25, ≥ 25- < 30, > 30, > 35, > 40)Extreme weight gain during pregnancySmoking statusRelevant medicationSocio economic status (income and education)

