### Statistics

#### Power calculation

There is no current information on what effect an increased vitamin D intake will have on the prevalence of preeclampsia or any of the other pregnancy complications of interest. Hence we have based our power calculation on a hypothesis of a 50–55% reduction in the prevalence of PE which we except to be the least common of the main targets, PE, FGR and GDM.

We expect a prevalence of PE of > 4% among the pregnant women getting the 10 µg vitamin D based on a prevalence of 4.1% in our previous study [17] with inclusion mainly during the summer months, hence the prevalence of PE will probably be a little higher when inclusion is done during both winter and summer months.

With a presumed prevalence of PE at > 4%, a significance level of 0.05 and a power of 80% then 1,000 women in each group will be sufficient to show a statistically significant difference between the two interventions despite a dropout of 5%. The entire study sample will be 2,000 women.

To test the hypothesis, that all participants in the intervention group reach a sufficient 25(OH)D level (≥ 75 nmol/L), a power calculation show that 15 women are needed in each group. The calculation is done with a power of 80% and a significance level of 0.05 and a presumed prevalence of 42% vitamin D insufficiency (25(OH)D < 75 nmol/L) before the intervention, based on data from our previous study [17]. Hence, we have chosen to take a second blood sample in the 3rd trimester in half of the cohort, resulting in 500 in each group.

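### The only covariate-adjusted model named is linear regression, placed with the binary outcomes and apparently tied to observed baseline differences; it does not directly give the planned relative risks

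*Protocol article*

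**What the plan says.** All of this stands in one paragraph of the protocol article, Statistical analysis, in this order:

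1. PE, FGR and GDM are analysed by "comparing the event rates in the two groups using a chi-square test and results will be presented as absolute and relative risks", with 95% confidence intervals.
2. "A similar approach will be used for categorical secondary outcomes".
3. "A multiple linear regression model will be used to adjust for indifferences in baseline characteristics".
4. 25(OH)D and the continuous secondary outcomes are compared by t-test.
5. "Linear regression models will be used to assess continuous variables such as serum levels, blood pressure and biological changes in the placentas".

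The article names no logistic, log-binomial or Poisson model. The word 'indifferences' in item 3 reads as a slip for 'differences'.

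The Power calculation section sets the level of risk. It expects PE above 4% in the 10 µg group (4.1% in the group's previous study), under "a hypothesis of a 50–55% reduction in the prevalence of PE".

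**The concern.** Item 3 comes after the binary outcomes and before any continuous one. If it were meant for continuous outcomes only, it would largely duplicate item 5. An analyst who followed the paragraph in order would fit ordinary least squares to 0/1 outcomes.

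Three things follow:

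- **Scale.** The unadjusted results are to be given as absolute and relative risks. The linear coefficient is a risk difference, so the adjusted and unadjusted results would not line up on the relative scale without a step that the article does not plan.
- **Fit.** At risks of 2–4%, an additive model can assign negative risks to women with favourable covariates.
- **Choice of covariates.** Adjusting for what differs at baseline makes the model depend on chance imbalance rather than on prognosis. A strong predictor of PE could be left out because it happens to balance, and a weak one taken in because it does not.

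**Working it through.** **The plan's own figure.** The sample size serves here only to fix the level of risk. With a control risk of 4%, a 55% reduction gives 0.04 × 0.45 = 0.018. The usual formula, two-sided 0.05 and 80% power, is

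n = [1.96·√(2p̄(1−p̄)) + 0.842·√(p₁(1−p₁) + p₂(1−p₂))]² / (p₁−p₂)², with p̄ = 0.029.

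This gives 913 per group, and 913/0.95 = 962 after 5% dropout. The stated 1,000 per group is therefore reproduced at the 55% end (power 81.6% with 950 evaluable per group). At the 50% end it is not: 1,141, or 1,202 after dropout. That is a separate matter. For the present point, PE risk is about 4% in controls and 1.8% to 2.05% (0.041 × 0.50) under the higher dose.

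**What the linear model estimates.** Fit Y = β₀ + β₁T + β₂X₁ + β₃X₂, where Y is 0/1 and T is the arm. Then β₁ is an adjusted risk difference. A relative risk needs a further step: average the fitted values with every woman set to T = 1, and divide by the average with every woman set to T = 0. In the intervention arm the mean fitted risk is about 2%, so a woman whose covariates place her more than about 2 percentage points below the arm average gets a negative fitted risk.

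**Simulation.** There were 1,000 trials per row, with n = 2,000, 1:1 allocation and a true relative risk of 0.5. The two covariates are assumptions, not figures from the article: one standard normal, one binary with 45% prevalence. RD is the risk difference and RR the relative risk.

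| Control risk | Assumed ORs (per SD; binary) | Negative fits, all women | Trials with any | Mean RD (true) | 95% CI coverage | RR, linear + standardisation | RR, robust Poisson |
|---|---|---|---|---|---|---|---|
| 4.1% | 1.0; 1.0 | 0.1% | 16.7% | −0.0206 (−0.0205) | 95.5% | 0.491 | 0.491 |
| 4.1% | 1.3; 1.5 | 1.9% | 73.9% | −0.0205 (−0.0205) | 94.1% | 0.495 | 0.495 |
| 4.1% | 1.5; 2.5 | 7.3% | 98.8% | −0.0205 (−0.0205) | 94.6% | 0.495 | 0.496 |
| 4.1% | 1.8; 2.5 | 10.6% | 100% | −0.0208 (−0.0205) | 94.9% | 0.488 | 0.488 |
| 10% | 1.5; 2.5 | 5.6% | 99.9% | −0.0501 (−0.0500) | 96.2% | 0.497 | 0.497 |

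Coverage is with ordinary standard errors; robust ones differ by 0.1 percentage point at most.

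A second set-up used 950 per arm, 4.0% against 1.8%, ORs of 2.5 for nulliparity and 1.08 per BMI unit, a BMI SD of 5 and 45% nulliparous (covariate figures all assumed). The median share of negative fits was 15% in the intervention arm, and about 8% of women in both arms together. The mean risk difference was −0.0218 against a true −0.0220, with 96% coverage. With ORs of 1.5 and 1.05, the intervention-arm median fell to 1.7%.

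**Reading of the results.** Negative fitted risks are common once covariates are moderately prognostic, but their number depends on assumed effects. They do not carry over into the treatment contrast.

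**The case against.** The case on the other side is substantial.

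- **The target is inferred.** The sentence names no outcome and could be meant for continuous ones. This stands as a limit. Position and the near-duplication with the later sentence favour the binary reading but do not prove it. On either reading, linear regression is the only adjusted model named.
- **The primary analysis is not touched.** PE, FGR and GDM are compared unadjusted, with risks and intervals. This stands, and it makes the adjusted model supplementary.
- **A reader might infer that relative risks cannot be had from this model.** They can: standardising the linear fit gave values within 0.001 of robust Poisson. They do not come directly, and the step is not planned. The risk difference itself fits the absolute scale, which is also planned.
- **A reader might infer that negative fitted risks spoil the treatment estimate.** They do not: the risk difference was nearly unbiased and coverage was 94–96%.
- **A reader might infer that covariates will be picked by significance tests.** No such rule is written. Screening ten independent variables at 0.05 would flag at least one with probability 1 − 0.95¹⁰ = 0.40, but both the ten and the screen are hypothetical.
- **Not all the outcomes are rare.** The Background puts GDM at 7–10% worldwide, and FGR is defined at the 10th percentile. Low risk describes PE best.
- **A covariate list may be left to a fuller document.** That is fair, and its absence is not the point. The point is what the article does state: a model, and a reason for adjusting that rests on observed differences.

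**Conclusion.** The point holds as a should-fix on a supplementary analysis. As worded, the article offers only linear regression for adjustment, in a position that attaches it to the binary outcomes. That model yields a risk difference and not, without further work, the planned relative risk. At PE risks of about 2–4% it can give negative fitted risks for roughly 0–11% of all women. That range rests wholly on the assumed covariate effects, and the treatment risk difference and its interval remain approximately valid.

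The tie to observed baseline differences is the more consequential part, because it leaves the adjusted model open until the data are seen. It rests on reading 'indifferences' as 'differences'.

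The documents do not support the stronger conclusion that the main comparison of PE, FGR or GDM is invalid.

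**What to change.** Replace the sentence with wording to this effect:

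- Adjusted relative risks and risk differences for binary outcomes come from Poisson regression with robust variance, or from logistic regression with standardisation.
- Covariates are chosen in advance on prognostic grounds and used whatever the observed balance. Candidates already collected are baseline 25(OH)D, BMI, parity, smoking and season of enrolment; the first four are already listed as subgroup factors.
- Linear regression is kept for continuous outcomes, and the word 'indifferences' is corrected.

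The cost is analysis wording and a little programming. No new data are needed. The change should be made before unblinding.

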### Randomisation and blinding

Randomisation is done in a 1:1 ratio, using Research Randomizer (version 4.0). To avoid skewering of data randomisation is done for 200 numbers a time. To assure an even distribution in the two intervention groups trough out the year to secure even distribution of season and hence sunshine exposure, the project supplements are packed in batches of 100 containers with 50 containers with placebo and 50 containers with vitamin D supplements. This is being repeated 10 times in total (n = 2,000). The containers with vitamin D supplement and those with placebo are identical and they are all marked with a unique number referring back to the randomisation. When a woman is included in the trial she will get a random container with tablets. The intervention is blinded for the participants and for all health professionals treating the women during their pregnancy and delivery. Only certain members of the research group, with no role in treatment and diagnosing the women, have access to the master list of randomisation numbers. Unblinding is permissible if a participant develops signs of Vitamin D intoxication and hypercalcemia.

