### Data collection methods

#### Blood samples

Venous blood samples will be collected at inclusion. For half of the participants a venous blood sample will be collected in their 3rd trimester as well. Blood samples will be analysed for 25(OH)D at Department of Clinical Biochemistry, Aarhus University Hospital, Denmark using HPLC–MS/MS, which is considered as the gold standard method for measurement of 25(OH)D [41]. Blood samples will also be analysed for calcium, phosphate, iron, zinc and HbA1c at Department of Clinical Biochemistry, Randers Regional Hospital, Denmark.

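### The named comparison of 25(OH)D is an unadjusted t-test; a prespecified ANCOVA on inclusion 25(OH)D and season would be more precise at almost no cost

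*Protocol article*

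**What the plan says.** The Statistical analysis section ties 25(OH)D to one test: "The 25(OH)D level will be assessed by comparing the mean in the two groups using students t-test". The chi-square sentence in that section covers pre-eclampsia, growth restriction and gestational diabetes, and is extended to categorical secondary outcomes. It does not mention 25(OH)D.

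Two further sentences in the section mention regression. Just before the t-test: "A multiple linear regression model will be used to adjust for indifferences in baseline characteristics". Shortly after it: "Linear regression models will be used to assess continuous variables such as serum levels, blood pressure and biological changes in the placentas". Neither lists covariates, and neither is ranked against the t-test. The section also allows a log transformation, to be decided from QQ-plots.

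Elsewhere the article describes what an adjusted analysis would use:

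- Blood samples, on the baseline draw: "Venous blood samples will be collected at inclusion". A second draw is planned for half the women, in the third trimester. On the assay, the section says: "Blood samples will be analysed for 25(OH)D at Department of Clinical Biochemistry, Aarhus University Hospital". Enrolment 25(OH)D is also a planned subgroup factor, so the inclusion samples are clearly meant to be assayed.
- Randomisation and blinding: containers are packed 50 placebo and 50 vitamin D per batch of 100, "to secure even distribution of season and hence sunshine exposure".
- Power calculation: 15 women per group are said to be needed for the 25(OH)D hypothesis, and the second sample is taken in half the cohort, "resulting in 500 in each group".
- Abstract and Outcome: the primary 25(OH)D outcome is a threshold at 75 nmol/L (at or above in the abstract, strictly above in the outcome list).

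**The concern.** Each woman with a third-trimester value should also have an inclusion value, measured by the same method. The Background treats seasonal sunshine as a major difficulty for vitamin D trials, and the packing is arranged to even it out between arms. A two-sample t-test uses neither. It leaves in the error term the variation that inclusion 25(OH)D and season could explain. It also cannot correct a chance difference in inclusion 25(OH)D between the arms of the sampled half.

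The regression sentences leave a second gap. With an unadjusted test, one or two regressions without covariates and a transformation chosen from the data, the article does not fix which 25(OH)D result will be reported as the main one. A log transformation would also change the effect measure, from a difference in means to a ratio of geometric means.

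At stake are the width of the interval, its robustness to chance imbalance, and precision in the subgroups. The Discussion relies on those subgroups to say which women need a higher dose.

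**Working it through.** **1. The plan's own figure.** Inputs from Power calculation: 42% insufficient against 0%, significance level 0.05 (two-sided assumed), power 80%.

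Pooled formula, with mean proportion 0.21:

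n = [1.96·√(2·0.21·0.79) + 0.8416·√(0.42·0.58 + 0)]² / 0.42² = (1.129 + 0.415)² / 0.1764 ≈ 13.5, so 14 per group.

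Exact power of Fisher's test is 77.0% at 14 and 82.6% at 15 per group. The stated 15 reproduces. It is a calculation for proportions, and 500 per group far exceeds it.

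**2. Inputs for the precision check.** The article gives neither an SD for 25(OH)D nor a correlation between inclusion and third-trimester values. Assumed: r = 0.3 to 0.6 and SD = 25 to 30 nmol/L. Women per arm: 500 × 0.95 = 475, borrowing the 5% dropout that the article states for the pre-eclampsia calculation.

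**3. Variance after adjustment for the inclusion value.** The residual variance factor is 1 − r², and the interval width factor is √(1 − r²).

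| r | 1 − r² | Variance removed | Width factor | Equivalent n per arm, 475/(1 − r²) |
|---|---|---|---|---|
| 0.3 | 0.91 | 9% | 0.954 | 522 |
| 0.5 | 0.75 | 25% | 0.866 | 633 |
| 0.6 | 0.64 | 36% | 0.800 | 742 |

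**4. 95% CI half-width in nmol/L.** Half-width = 1.96 × SD × √(2/475) × √(1 − r²), with √(2/475) = 0.0649.

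| SD | Unadjusted | r = 0.3 | r = 0.5 | r = 0.6 |
|---|---|---|---|---|
| 25 | 3.18 | 3.03 | 2.75 | 2.54 |
| 30 | 3.82 | 3.64 | 3.30 | 3.05 |

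The narrowing is about 5% at r = 0.3 and 20% at r = 0.6. Any gain from season terms is extra and cannot be sized from the article.

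**5. Power for the main comparison, 500 per arm.** For a difference of 0.3 SD, unadjusted power is already 99.7%. For 0.2 SD it is 88.5% unadjusted, 91.2% at r = 0.3 and 95.5% at r = 0.5. Adjustment changes power materially only for differences of about 0.2 SD or less.

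**6. Subgroups.** Detectable difference at 80% power = (1.96 + 0.84) × √(2/n) × √(1 − r²), in SD units. For an illustrative 50 women per arm, this is 2.80 × 0.20 = 0.56 SD unadjusted and 0.56 × 0.8 = 0.45 SD at r = 0.6. In subgroups defined by enrolment 25(OH)D itself the gain would be smaller, because the inclusion value varies less within each band.

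**The case against.** The strongest reply is that the article does plan adjustment. One sentence promises multiple regression for baseline differences, another promises linear regression for serum levels, and enrolment 25(OH)D is a subgroup factor. The covariate list and the ranking of models are ordinary content of an analysis plan, which is not shown. The t-test is valid in a randomised comparison, and ignoring a balancing factor errs on the cautious side. With 500 per arm, an interval narrower by less than 1 nmol/L is unlikely to change a conclusion about 90 µg against 10 µg.

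Much of this stands, and it rules out several stronger readings:

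- A reader might infer that the baseline measurements are thrown away, or that a baseline imbalance must carry into the result. The regression sentences leave room for adjustment, so the article does not support that.
- A reader might infer that the comparison is biased or underpowered. It is neither.
- A reader might infer that the plan itself names inclusion 25(OH)D and batch as the main sources of variation. It names sunshine and season as a major challenge, and also latitude, skin tone and adiposity. It does not say this of the inclusion value or of batch.
- A reader might take the t-test as the test of the primary outcome as defined. That outcome is a threshold, whereas the t-test compares means.

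Batch packing balances season of enrolment for all participants. In the half who are sampled again, months later, the balance is only approximate.

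The reply does not remove the point. The complaint is not that a covariate list is missing. The article states a method, and that method is less efficient than one available from the same data. The sentence on baseline differences follows the categorical outcomes, names no outcome, and reads as adjustment for imbalances once seen. The sentence on serum levels names neither arm, inclusion value nor season. Neither amounts to a prespecified ANCOVA.

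**Conclusion.** The point holds as one of efficiency and prespecification, not of validity. The only between-arm test that the article names for 25(OH)D is unadjusted, and it does not say whether that test or a regression is primary.

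For an assumed correlation of 0.3–0.6, the t-test forgoes a 9–36% reduction in variance, which is 5–20% of the interval width. In nmol/L, under the assumed SD of 25–30 and 475 per arm, the most favourable case in that range is a half-width of 2.5–3.1 instead of 3.2–3.8. These sizes rest on assumed values. The direction does not: any nonzero correlation gives some gain at this sample size, apart from a negligible loss of degrees of freedom.

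The main comparison will not fail for lack of power. The benefit is a tighter interval, protection against chance baseline imbalance, more useful subgroup estimates and a single declared analysis. The change is worth making because it is nearly free.

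**What to change.** In Statistical analysis, name one primary comparison of mean third-trimester 25(OH)D: ANCOVA on arm, inclusion 25(OH)D, and randomisation batch or season of enrolment, with month of third-trimester sampling added if wanted. Fix the scale (nmol/L or log) in advance instead of choosing it from QQ-plots. Keep the t-test as a supportive analysis. State whether the two general regression sentences refer to this model or to something else.

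Because the primary outcome is a threshold, add a binary model for the proportion at 75 nmol/L or above with the same covariates, and use one definition of the threshold throughout. The planning hypothesis is that every woman in the intervention group reaches sufficiency. An arm with no insufficient women would make an ordinary logistic model fail to converge, so name a fallback in advance, such as an unadjusted risk difference with an exact interval.

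The cost is wording, in the analysis plan or an amendment. Inclusion 25(OH)D is already to be assayed, and batch and dates should be available from the container numbers and planned visits. No extra samples or participants are needed.

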## Discussion

The current recommendation regarding vitamin D in pregnancy in Denmark is based on a few small and older observational studies from other Northern countries with a diet that differs from the typical Danish diet when it comes to vitamin D containing food items such as fatty fish and the use of fish oil supplements. Since this recommendation was made a lot of new evidence have indicated that vitamin D has several additional beneficial effects in pregnancy than just bone development. New recommendations are therefore needed to fit the pregnant population today with an emphasize on the dietary habits, ethnicity and health status of today's population.

With this randomised trial it will be possible to determine if a higher intake of vitamin D in pregnancy can improve the health for pregnant women and their children, by preventing maternal and neonatal complications also associated with health risks in later life. The trial is designed with a statistical power to determine the effect of a higher vitamin D supplement on the risk of developing the major obstetric diseases related to placental dysfunction – PE, FGR and GDM. Such diseases can possibly be prevented for some women by taking an extra vitamin D supplement in pregnancy – a period where most women are already vigilant when it comes to their diet and use of supplements. Further, the trial is large enough to establish if all pregnant women need to take more vitamin D to avoid deficiency or if only some groups of pregnant women need higher doses of vitamin D in their pregnancy e.g. women suffering from overweight or obesity.

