Our trial has some limitations. We reach the pregnant women at their first contact to the hospital, hence they are in gestational week 9–14 when enrolled in the trial and starting the intervention. As this is still several weeks before complications like PE, GDM and FGR occur, we would argue that this is not too late in pregnancy to initiate the intervention with a higher dose of vitamin D supplementation. Initiation of the intervention already before conception would most likely lead to a better effect of extra vitamin D. However, such a trial design would demand a vastly larger study population as the drop-out and lost-to-follow-up would be much higher. Furthermore, it would be challenging to reach enough women before conception and have them agree to participation in a trial. Therefore, such a trial design would be much more expensive and difficult to conduct, and a trial design like ours is a good alternative as initiation of the intervention is still in the first third of the pregnancy. Another limitation to the trial is the lack of skin type measurement. Skin type could have been evaluated using the Fitzpatrick visual scale, however as this is a visual scale it has certain limitations. Evaluation using the scale would rely on the print of the scale or light in the screen if used electronically. The best way to measure skin type would be by using a device measuring chromaticity unfortunately such a device was not available in this trial. Ethnicity of the participants are evaluated according to the origin of their parents and this will be used as a proxy of their skin type. The trial is conducted as a single-centre study which leads to both strengths and limitations. A strength is the complete alignment in diagnosing and treatment of the women as they are all followed by the same staff of midwifes and doctors and all give birth at the same labour ward with only a very few exceptions. However, a limitation always related to single-centre studies is the question of whether the study population is representative for a larger population. The trial takes place at a hospital covering both urban and rural areas and people from all socioeconomic groups and represent a broad sample of the entire population in Denmark. Selection bias can of course not be excluded completely. It is possible that people of a lower socioeconomic status with more limited resources might be more prone to decline participation in a clinical trial. On the other hand, it cannot be excluded that the offer of free vitamins will influence the decision towards acceptance of attendance among women with limited economic resources. There is also a risk that we might miss a larger proportion of women with a high interested in health matters e.g. older women who have struggled to become pregnant as these women might wish to remain in full control of their vitamin D intake. However, if the trial shows a beneficial effect of higher doses of vitamin D supplementation, initiated after pregnancy is determined this effect would especially be most beneficial to high risk groups including vulnerable pregnant women with lower socioeconomic status and those who have a higher risk of adverse maternal and neonatal outcomes. As both health care workers and many pregnant women themselves rely on the official recommendations for their health choices in pregnancy, results from this trial can help decision makers to make a new and more accurate recommendation concerning the ideal dose of vitamin D supplementation in pregnancy and in this way reach the majority of the pregnant population.

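### Two of the eight planned subgroup variables are badly specified: the BMI bands overlap and leave gaps, and gestational weight gain is mostly a post-randomisation variable

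*Protocol article*

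**What the plan says.** The Statistical analysis section lists eight subgroup variables: 25(OH)D at enrolment, parity, ethnicity, BMI, extreme weight gain in pregnancy, smoking, relevant medication and socioeconomic status. For BMI it prints the cut-offs "≥ 20- < 25, ≥ 25- < 30, > 30, > 35, > 40". It does not say that the last three are meant to be cumulative.

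The Exclusion criteria cover age, consent, gestational age, calcium metabolism, kidney disease and physician-initiated vitamin D treatment. None concerns BMI, so women of any BMI can be enrolled.

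On timing, the Discussion says of the women that "they are in gestational week 9–14 when enrolled in the trial and starting the intervention".

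The Discussion also says what such analyses should deliver. With prevention of deficiency as the goal, it considers the trial big enough to settle whether extra supplementation is needed by everyone or by some. It words the second possibility as follows: "if only some groups of pregnant women need higher doses of vitamin D in their pregnancy e.g. women suffering from overweight or obesity".

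**The concern.** BMI is the article's own example of a factor that might separate women who need more vitamin D from those who do not, and the Background names adiposity as a cause of deficiency. A subgroup variable with that role should place each enrolled woman in exactly one band, so that a single interaction test can ask whether the treatment effect differs by BMI. The printed cut-offs do not do this.

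Weight gain raises a different problem. A subgroup comparison is protected by randomisation only if membership is settled before treatment starts. Total weight gain is not. It also reflects events that the trial counts as outcomes, so arms compared within a weight-gain stratum may no longer be comparable. Such a comparison could show a difference that is not there or hide one that is.

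**Working it through.** The article gives no figure for any subgroup, so there is nothing to reproduce, and its sample size of 1,000 per arm is not in question here.

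**BMI.** Applying the printed inequalities to test values gives:

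| BMI | Bands that contain it | Number |
|---|---|---|
| 18, 19.9 | none | 0 |
| 20, 24.9 | 20 to < 25 | 1 |
| 25, 29.9 | 25 to < 30 | 1 |
| 30 | none | 0 |
| 30.1, 35 | > 30 | 1 |
| 36, 40 | > 30, > 35 | 2 |
| 41, 42 | > 30, > 35, > 40 | 3 |

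A factor needs a count of 1 in every row. Here the count runs from 0 to 3, for two reasons:

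- *Gaps.* Below 20 there is no band. At 30 the second band stops short of the value and the third starts just above it.
- *Nesting.* > 40 lies inside > 35, which lies inside > 30. Every woman above 40 therefore contributes to all three obesity estimates, and these are not independent of one another. If the five bands were entered in one model as five indicators, the reference group would be whoever scores zero on all of them, which is the women below 20 together with those at exactly 30.

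The first three bands taken alone (20 to < 25, 25 to < 30, > 30) share no women. If BMI is a baseline value, each gives a randomised comparison, and the three can form one interaction test.

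The number of women left out cannot be derived, because the article gives no BMI distribution. Purely as an assumption, if 5–15% have a BMI below 20, then 0.05 × 2,000 = 100 to 0.15 × 2,000 = 300 women would have no BMI band.

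**Weight gain.** Treatment starts in gestational week 9–14. The secondary outcomes define preterm birth as before 37 weeks and post-term birth as after 40, so take births at 37 and at 40 weeks:

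- Birth at 40 weeks: (40 − 14)/40 = 65% to (40 − 9)/40 = 78% of the pregnancy follows the start of treatment.
- Birth at 37 weeks: (37 − 14)/37 = 62% to (37 − 9)/37 = 76%.

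These are shares of time, not of kilograms, but they show that the classification cannot be made at enrolment.

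Several outcomes in the article can also move a woman into or out of the stratum: preeclampsia through oedema, gestational diabetes through dietary management, fetal growth through fetal weight, and preterm birth through a shorter time in which to gain. Membership then depends partly on the result being compared. The direction of the resulting bias cannot be stated in advance.

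**The case against.** The strongest reply has four parts.

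- **Much of the subgroup plan is sound.** A reader might infer that the planned subgroups as a whole cannot show which women need the higher dose. That does not follow. Six of the eight variables are untouched by these points. Enrolment 25(OH)D is a baseline variable, and its three strata are complete and non-overlapping if the middle one includes both ends. The article is not uniform on whether sufficiency means at least 75 or above 75 nmol/L, but that is a separate matter to reconcile. This part of the reply stands.
- **BMI can still be examined.** A reader might infer that no valid test by BMI is possible, or that women above 40 are triple-counted in some total. Neither is supported. The bands 25 to < 30 and > 30 cover the overweight and obese women named in the Discussion, apart from the single value 30. The cut-offs > 35 and > 40 can be read as cumulative, and no planned analysis adds the bands together. This stands too, but the article does not state the cumulative reading, and that reading still leaves out women below 20.
- **The Discussion sentence is about avoiding deficiency, hence 25(OH)D.** The outcome-driven contamination of weight gain bears mainly on the clinical outcomes. For 25(OH)D the disjoint bands may serve well: assuming 42% versus 10% below 75 nmol/L and 475 evaluable women per arm, a band holding 10% of them has about 96% power. This limits the damage. However, the subgroup list is not confined to 25(OH)D, and weight gain is unknown at enrolment whatever the outcome.
- **A separate analysis plan may add detail.** It may define extreme gain or specify the interaction model, and neither is held against the article. But the cut-offs and the weight-gain subgroup are stated here, so a later document would have to contradict them to repair them.

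**Conclusion.** The point holds for two of the eight subgroup variables. As printed, the five BMI bands are not a partition and cannot serve as separate levels of one treatment-by-BMI interaction test. The weight-gain subgroup is defined mostly after randomisation, is open to bias from treatment and outcomes, and cannot identify women at enrolment. This weakens the stated aim for women with overweight or obesity but does not defeat it, because three of the BMI bands remain comparable.

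The band mapping follows from the text without assumptions. The 100–300 women without a band rest entirely on an assumed 5–15% share and should not be read as an estimate. Those women would be missing only from the BMI breakdown; they remain in the intention-to-treat analysis of every outcome, so no primary result is affected. The correction should be made, but it concerns subgroup analyses only.

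**What to change.** - State that BMI is the pre-pregnancy or enrolment value, and use exhaustive, non-overlapping bands, for example < 20, 20 to < 25, 25 to < 30, 30 to < 35 and ≥ 35. Each BMI then falls in exactly one band. If the sponsor wants to keep the highest cut-off, ≥ 40 can be shown separately as a descriptive subset of the top band.
- Assess effect modification by BMI with one treatment-by-BMI interaction test. With five bands it has 5 − 1 = 4 degrees of freedom.
- Remove extreme weight gain from the subgroup list, or report weight gain by arm as a post-randomisation outcome.

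The change is one of wording and should be made before unblinding, so that the bands are not chosen with results in view. It needs no data beyond what the BMI subgroup already requires. The cost is the loss of one exploratory subgroup; the sample size and primary analyses stay as they are.
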